## Abstract

**Background:**

Fecal incontinence (FI) is defined as the recurrent involuntary excretion of feces in inappropriate places or at inappropriate times. It is a major and highly embarrassing health care problem which affects about 2 to 24% of the adult population. The prevalence increases with age in both men and women.

Physiotherapy interventions are often considered a first-line approach due to its safe and non-invasive nature when dietary and pharmaceutical treatment fails or in addition to this treatment regime. Two physiotherapy interventions, rectal balloon training (RBT) and pelvic floor muscle training (PFMT) are widely used in the management of FI. However, their effectiveness remains uncertain since well-designed trials on the effectiveness of RBT and PFMT versus PFMT alone in FI have never been published.

**Methods/Design:**

A two-armed randomized controlled clinical trial will be conducted. One hundred and six patients are randomized to receive either PFMT combined with RBT or PFMT alone. Physicians in the University Hospital Maastricht include eligible participants. Inclusion criteria are (1) adults (aged ≥ 18 years), (2) with fecal incontinence complaints due to different etiologies persisting for at least six months, (3) having a Vaizey incontinence score of at least 12, (4) and failure of conservative treatment (including dietary adaptations and pharmacological agents). Baseline measurements consist of the Vaizey incontinence score, medical history, physical examination, medication use, anorectal manometry, rectal capacity measurement, anorectal sensation, anal endosonography, defecography, symptom diary, Fecal Incontinence Quality of Life scale (FIQL) and the PREFAB-score. Follow-up measurements are scheduled at three, six and 12 months after inclusion. Skilled and registered physiotherapists experienced in women's health perform physiotherapy treatment. Twelve sessions are administered during three months according to a standardized protocol.

**Discussion:**

This section discusses the decision to publish a trial protocol, the actions taken to minimize bias and confounding in the design, explains the choice for two treatment groups, discusses the secondary goals of this study and indicates the impact of this trial on clinical practice.

**Trial registration:**

The Netherlands Trial Register ISRCTN78640169.

## Background

### Background of fecal incontinence

Fecal incontinence (FI) is a major health care problem, that is particularly embarrassing and affects about 2 to 24% of the adult population, increasing to 47% in the institutionalized elderly [1-7]. The actual prevalence is likely to be higher due to the common underreporting of FI as a result of patients' embarrassment to visit a physician or unawareness of possible treatment options [8]. FI can be defined as the recurrent involuntary excretion of feces in inappropriate places or at inappropriate times [7], and covers a wide spectrum from involuntary but recognized passage of gas, liquid, or solid stool (urge incontinence) to unrecognized anal leakage of mucus, fluid, or stool (passive incontinence) [9]. Fecal continence is based on a combined interplay of sensory, motoric and reservoir functions. Incontinence occurs if one or more of these components fail and when compensatory mechanisms fall short. Obstetric trauma is one of the major causes of FI in women. Several colorectal, urological or gynaecological interventions can cause FI as well. Specific neurological diseases associated with FI include diabetes, multiple sclerosis, Parkinson's disease, stroke, and spinal cord injury.

FI is often thought to be associated with older people, as a natural aspect of ageing. Recently, it has been estimated that 6% of the persons aged 60 years and older suffer from involuntary loss of feces and 3% from involuntary loss of both feces and urine [8]. In addition, the prevalence of FI will increase in the next fifteen years due to double ageing. However, younger patients are often affected as well [1]. FI interacts with multiple aspects of daily life resulting in a number of difficulties; having to stay at home near a toilet, having to avoid social contacts including relationships or sexual contact, having feelings of depression and low self-esteem [2]. Moreover, it is often difficult to explain experiencing FI to others, like family or a partner. A lot of these implications are due to the unpredictable character of FI and the fear of odour or soiling [10].

Apart from a social burden to the patient, FI also has a significant impact on the health care budget. Limited data are available on healthcare costs for FI [9,11]. Recently, total costs in the Netherlands were estimated at € 2169 per fecally incontinent patient a year [12].

Estimates of health care costs and prevalence numbers for FI vary greatly and depend on the clinical setting and on the definition of FI based on severity and frequency [1,13,14].

### Physiotherapy in fecal incontinence

Treatment of fecally incontinent patients consists of conservative as well as surgical interventions. Surgical interventions aim to anatomically and functionally correct the rectum, anus, pelvic floor or anal sphincters. Conservative interventions consist of dietary adaptations, medication, absorbent materials, and physiotherapy. Physiotherapy interventions are non-invasive and inexpensive, require no sophisticated equipment and have hardly any adverse effects. Besides, physiotherapy does not exclude any other form of treatment [15]. Therefore, physiotherapy is often attempted before surgical treatment.

Physiotherapy FI management includes pelvic floor muscle training (PFMT), biofeedback (BF), rectal balloon training (RBT) and electrical stimulation (ES). PFMT aims to restore muscular strength, coordination and timing of contractions. With BF the patient gets information about the activity of the pelvic floor muscles by way of a visual display. RBT, as a modality of BF, is used to decrease the sensory threshold in case of passive FI and to increase the sensory threshold in case of urge FI. In addition, RBT aims to synchronize contraction of the external anal sphincter with relaxation of the internal anal sphincter. ES is used to increase awareness and isolated contraction of the anal sphincters. Often, one or more physiotherapy interventions are combined, depending on the underlying cause of FI.

Over 60 uncontrolled trials exist on the use of biofeedback for the management of FI [16]. Some authors conclude that biofeedback is the treatment of choice for FI on the basis of these observational studies [17]. An overall cure and improvement rate of 72 percent has been reported [18]. However, the results of a Cochrane review on the effects of BF and/or PFMT for the treatment of FI in adults were based on eleven randomized controlled but heterogeneous trials and showed that some elements of BF therapy and sphincter exercises might have a therapeutic effect, but this is not certain [16]. Moreover, it was suggested that RBT improved continence more than sham training. This is in agreement with other authors who consider lowering the threshold volume for discrimination of rectal distension an important factor in the success of BF [15,19-21].

In an attempt to assess the effect of the different BF components (balloon/pressure BF, electromyographic BF) in the management of FI, two complicated cross-over trials have been performed [15,20]. Group comparison was impossible to assess due to the small sample in one trial (16) and the single case experiments in the other (21).

A second Cochrane review evaluated ES in adult patients with FI [16,22]. Insufficient data was available to allow reliable conclusions on the effect of ES in the management of FI [22]. A recently published randomized controlled trial examined whether anal ES, in the absence of any adjunct exercises or advice, would improve symptoms more when compared with "sham" ES. It is concluded that 1 Hz (sham) was as effective as 35 Hz. Possibly, the main effect is not sphincter contraction but sensitization of the patient to the anal area, or simply the effect of intervening per se (Hawthorne effect) [23].

Finally, the results of a recent large cohort study on ES and PFMT with BF in patients with severe FI indicated that pelvic floor muscle rehabilitation leads to a modest improvement in severity of FI, squeeze pressure and maximal tolerated volume [24].

Although uncertainty exists on the exact extent of the effectiveness of physiotherapy treatment in FI, results are promising [18].

### Relevance

Evaluating effectiveness of physiotherapy treatment has been impeded by lack of enough quality studies, lack of standardization, a large variety in outcome measures and methodological flaws [25]. Ultimately, there is a need to evaluate treatment options in FI, especially since FI considerably reduces quality of life. Besides, FI has a significant impact on the health care budgets, and the prevalence of FI is increasing due to double ageing [26].

PFMT has been proven effective in the treatment of stress urinary incontinence [27]. Since the anal sphincter and puborectalis muscle form a part of the same pelvic floor as the closing urethral system, expectations are raised for the same positive results of pelvic floor muscle re-educative techniques in FI. Next to PFMT, some authors consider lowering the threshold volume for discrimination of rectal distension as an important factor in the success of physiotherapy [15,19-21]. No study has reported adverse events from either PFMT or RBT, and it seems unlikely that these treatments itself could cause symptoms to worsen.

Apparently, PFMT and RBT seem to have a role in the treatment of fecally incontinent patients. Since well-designed trials on the effectiveness of RBT and PFMT versus PFMT alone in patients with FI have never been published, a randomized controlled trial on this topic will be carried out (Physiotherapy in Fecal Incontinence Trial – PhysioFIT-study).

## Methods/Design

### Study design, research question and hypothesis

A two-armed randomized controlled clinical trial will be conducted in patients diagnosed with FI (Figure 1), serving the following research question: what is the effectiveness of rectal balloon training and pelvic floor muscle training compared to pelvic floor muscle training alone in patients with fecal incontinence?

**Figure 1 F1:**
[figure not shown]
**Flowchart of the PhysioFIT-study**. t = point in time; VS = Vaizey score; MH = medical history; M = medication use ; PE = physical examination; DI = diary; AM = anorectal manometry; RC = rectal capacity measurement; AS = anorectal sensation; AE = anal endosonography; D = defecography; FIQL = fecal incontinence quality of life scale; PREFAB = modified PRAFAB-score; GPE = Global Perceived Effect-score; PFMT = pelvic floor muscle training; RBT = rectal balloon training; VS (-) = reduction on VS < 4 points; VS (+) = reduction on VS ≥ 4 points; GPE (+) = score 1–7 on GPE scale; GPE (-) = score 8 or 9 on GPE scale

It is hypothesized that patients receiving the combined training will have a larger reduction on the primary outcome measure.

### Recruitment, informed consent and randomization

The medical ethics committee of the University Hospital Maastricht/Maastricht University approved the PhysioFIT-study. The physician points out during the first visit that the patient is eligible to participate in the trial. The patient is provided with patient information sheets and information on the diagnostic tests. Participating patients sign informed consent at the beginning of the second visit, allowing eligible participants two months to decide to participate.

An independent research assistant performed the blocked randomization (size of four). A computer-generated randomization list is prepared in advance. The independent research assistant contacts the physiotherapist by telephone to inform about the referral and the allocated treatment.

### Blinding

The research doctor, performing the general diagnostics, and the researcher, dealing with the data-entry, are blinded during baseline measurements but not during follow-up measurements. However, the physician involved in measuring the primary outcome measure is blinded and blinded double data-entry is performed to assure correct data-entry. It is impossible to blind patients and participating physiotherapists for treatment allocation. However, physiotherapists are not involved in the diagnostic work-up and follow-up measurements. The outcome assessors are blinded.

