▪ PREFAB-score: the PREFAB-score is a modified version of the widely used and accepted PRAFAB-score in the urinary incontinence field. The PRAFAB-score is a simple and quickly obtained score which summarizes several objective and subjective components of the severity of urinary incontinence complaints (ranging from 5–20) [33]. The score has proven to be reliable, valid and responsive [34]. Since most of the PRAFAB-score, except for the "amount" item, is applicable to fecally incontinent patients as well, it is suggested to adapt the PRAFAB-score to fecally incontinent patients. From the patients' point of view, two aspects about excretion of feces are reported to be highly embarrassing and affecting social life and body image: whether the excretion can be held up by a pad or not and whether excretion can be smelled by the environment or not. These two aspects, reflecting social limitations, are therefore integrated in the modified PRAFAB-score (min-max = 6–20; range = 15).

▪ Global perceived effect (GPE) (Table 2): this subjective score reflects the change in complaints after physiotherapy treatment compared to the period before treatment and ranges from 1–9 points. A score of 8 or 9 indicates much worsening of complaints and is an indication to consider co-interventions.

**Table 2 T2:** Global perceived effect (GPE-score)

To which degree have your complaints changed compared to the period before physiotherapy treatment?
At the moment, the complaints are .....
1. Very much improved
2. Much improved
3. Moderately improved
4. Slightly improved
5. Unchanged
6. Slightly worse
7. Moderately worse
8. Much worse
9. Very much worse
..... compared to the period before physiotherapy treatment

Follow-up measurements are scheduled at 3, 6 and 12 months after inclusion. Primary outcome measure is the Vaizey score [28]. Success after physiotherapy is defined as a reduction in Vaizey score of more than four points (16.7%) compared to baseline measurement. Recently, it is reported that patients who rated their situation to be better, improved four points on the Vaizey score [31]. Secondary outcome measures are anorectal resting and squeeze pressure, rectal capacity, anorectal sensation, diary results, FIQL, PREFAB-score and GPE-score.

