### Referral

After diagnosis and inclusion, patients are referred to an extramural private practice, preferably nearby their home address. Private practices are selected with physiotherapists experienced in women's health, who are registered at the Dutch Society for Physical Therapy in Pelvic Floor Disorders and Pre- and Postnatal Healthcare (NVFB). They are all educated and trained in the performance of invasive techniques, as is used during digital testing and RBT. In total, 90 physiotherapists participate throughout the Netherlands. The initial physiotherapy session should be within three weeks after referral. The patient hands over an acknowledged doctor's referral letter and fifteen rectal balloons (group 1) to the physiotherapist before the initial session. FI is not recognized as a chronic disorder and insurance coverage is patient dependent. However, physiotherapy in this trial is considered as being part of usual care, as included patients would also be excellent candidates for physiotherapy outside the scope of this trial. Since January 2006 a referral letter is not obligatory anymore.

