### Bias and confounding

To minimize information bias, the performance of physiotherapists experienced in women's health is standardized. First, only physiotherapists registered at the NVFB are able to participate in this study. Registration approval indicates satisfying the outlined quality criteria by the NVFB. Second, participating physiotherapists receive a general and physiotherapy protocol of the PhysioFIT-study composed by experts in the field. Third, participating physiotherapists attend a general meeting. An individual visit is organised when a patient is referred to a non-attending physiotherapist. During the meeting, the physiotherapists were instructed on the general and physiotherapy protocol, a DVD-film illustrated the intended rectal balloon training and questions and discussions were raised. Some small adaptations were made in the protocol based on remarks from the physiotherapists.

To further minimize information bias, adaptations were made to the rectal balloons of the supplier. The current balloon reached the sigmoid colon, as soon as the balloon was filled with approximately 180 ml, possibly resulting in colic pains. This prevented the measurement of a higher maximal tolerated volume, although 180 ml is rarely reached. As this balloon was inadequate for this trial, adapted rectal therapy balloons were developed in cooperation with the supplier.

In this trial, it is impossible to blind on all levels. Most importantly, the measurement of the primary outcome is blinded as well as the outcome assessors. Blinded double data-entry is performed to assure correct data-entry.

Confounders that are taken into account are presence of urinary incontinence, use of anal tampons, patients' compliance and medication use. The presence of urinary incontinence can influence the perception of patients' quality of life and estimation of severity of FI, thereby distorting the scores on the FIQL, PREFAB and GPE-scores. Furthermore, patients' compliance to the home exercise program determines therapy intensity and indirectly therapy success. Therefore, the physiotherapist asks each session patients' compliance to the home exercise program as formulated. The patient gives an explanation in case of insufficient compliance. Finally, the use of anal tampons and medication use can influence the number of involuntary events and stool consistency, as measured during the visits to the physician and in the diary.

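### The outcome assessors are called blinded without qualification, yet the research doctor and the data-entry researcher are unblinded at follow-up, so on the natural reading the physiological secondary outcomes are assessed unblinded

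*Protocol article*

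**What the plan says.** All places are in the protocol article.

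- **Blinding**, on two named roles: "The research doctor, performing the general diagnostics, and the researcher, dealing with the data-entry, are blinded during baseline measurements but not during follow-up measurements".
- **Blinding**, next sentence, on the primary outcome and data handling: "the physician involved in measuring the primary outcome measure is blinded and blinded double data-entry is performed to assure correct data-entry".
- **Blinding**, on treatment: "It is impossible to blind patients and participating physiotherapists for treatment allocation". The section adds that physiotherapists take no part in the diagnostics or follow-up measurements.
- **Blinding**, closing sentence: "The outcome assessors are blinded".
- **Bias and confounding** (Discussion), after conceding that blinding at every level is impossible: "Most importantly, the measurement of the primary outcome is blinded as well as the outcome assessors".
- **Baseline and follow-up measurements**: "Secondary outcome measures are anorectal resting and squeeze pressure, rectal capacity, anorectal sensation, diary results, FIQL, PREFAB-score and GPE-score".
- **Recruitment, informed consent and randomization**: "An independent research assistant performed the blocked randomization (size of four"). The list is computer-generated in advance, and the assistant phones the allocation through to the physiotherapist.
- **Referral**: in the combined arm only, the patient brings "fifteen rectal balloons (group 1) to the physiotherapist before the initial session".

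**The concern.** Within one section, two people with a part in follow-up are said to be unblinded and all outcome assessors are said to be blinded. Both statements cannot hold if the research doctor carries out the follow-up diagnostics that yield secondary outcomes.

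The outcomes affected are those closest to what the experimental component is meant to change. The Rectal balloon training section describes work on sensory threshold, urge sensation and maximal tolerated volume. The rectal capacity measurement records the same three volumes. The operator applies the stimulus and records the volume at each endpoint, so an operator who knows the arm has some room to influence the result. A reader who relied on the blanket statement would give these results more protection from observer bias than the plan provides.

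A second, smaller matter is allocation. Treatment is open, one hospital recruits, and a single block size is used. If recruiting staff came to know earlier allocations, some later ones could be inferred, and inclusion could be influenced.

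**Working it through.** **Part 1: blinding, statement against statement**

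1. *Are the physiological tests follow-up outcomes?* Yes. Baseline and follow-up measurements lists pressures, rectal capacity and anorectal sensation as secondary outcomes. Data analysis compares secondary outcomes at baseline with those at 3, 6 and 12 months.
2. *Who performs them at follow-up?* This is not stated outright. The Blinding section ties the research doctor to the general diagnostics and, in the same sentence, says this doctor is not blinded during follow-up measurements. That remark has little point unless the doctor performs or handles measurements then.
3. *Does the blanket statement fit?* Given step 2, it does not fit the physiological secondary outcomes.
4. *Does it fit the primary outcome?* As far as the assessor goes, yes: a blinded physician is named. The items in Table 1 (episode frequencies, lifestyle, pad use, medication, ability to hold on) depend on what the patient reports, and patients know their arm. A blinded recorder is therefore documented; a blinded source is not, and cannot be.
5. *Data entry.* The researcher dealing with data entry is unblinded at follow-up, while double data-entry is called blinded. The two fit only if someone else makes the blinded entry, or if entry works from records without the arm. The article does not say which.

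No size can be put on observer bias from the document.

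**Part 2: predictability under a fixed block of four**

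Inputs: block size 4 (Recruitment section); total 106 (Sample size section). Equal allocation, two per arm in each block, is my assumption, since the ratio is not stated.

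The total of 106 only sets the scale, and it reproduces. With SDs 8.45 and 3.90, difference 17 − 13.67 = 3.33, one-sided 0.05 and 80% power:

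- n per arm = (8.45² + 3.90²)(1.645 + 0.842)² / 3.33² = 48.29
- total = 2 × 48.29 × 1.1 = 106.2

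There are 6 equally likely sequences of two A and two B. For an observer who knows all earlier allocations and where each block starts:

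| Position in block | Probability next allocation is certain | Probability best guess is right |
|---|---|---|
| 1 | 0 | 0.500 |
| 2 | 0 | 0.667 |
| 3 | 1/3 | 0.667 |
| 4 | 1 | 1.000 |

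- Share certain = (0 + 0 + 1/3 + 1)/4 = 8/24 = 33.3%.
- Mean correct guess = (0.5 + 0.667 + 0.667 + 1)/4 = 70.8%, against 50% by chance.
- 106 patients make 26 full blocks plus 2. Certain: 26 × 4/3 = 34.7, about 35. Correct guesses: 26 × 2.833 + 0.5 + 0.667 = 74.8, about 75.

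*Timing.* At the expected one patient a week (Trial arms and patient selection), a block fills in about 4 weeks. The first follow-up is at 3 months, about 13 weeks, and 13/4 is roughly 3 blocks. Unblinding at follow-up therefore comes too late to reveal the block in progress. Earlier knowledge would be needed, for example from seeing who carries balloons.

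**The case against.** The strongest reply has four parts.

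- **The primary outcome is protected.** A separate blinded physician is named for the Vaizey score, and blinded double data-entry is planned. This stands. A reader might infer that the claim of blinded primary measurement is simply false because patients are unblinded. The document does not support that: it openly says that patients cannot be blinded, and its claim can be read as one about the assessor. What remains is that the Discussion's wording is looser than the facts it rests on.
- **The research doctor's follow-up role is inferred.** General diagnostics is also the term used under Study population for the work-up before inclusion, and nobody is named for follow-up manometry. This stands as a limit on certainty. It does not remove the conflict, because the sentence explicitly concerns follow-up measurements.
- **The tests leave limited room for the examiner.** Inflation is in slow increments, the sensation endpoints come from the patient, and a computer-assisted polygraph is used. This reduces the risk of observer bias without making the assessor blinded.
- **No route to selection bias is documented.** A reader might infer from the block size and the balloons that recruiting staff can foresee allocations. The document does not show this. An independent assistant runs the randomization and informs the physiotherapist directly; treatment is given in outside practices; and nothing says who issues the balloons, or that the recruiting surgeons see them or learn any allocation. Patients may also take up to two months to decide, which makes it harder to steer a patient to a given slot. This stands, and it makes the allocation point conditional.

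**Conclusion.** The point holds for blinding. The unqualified statements in Blinding and in Bias and confounding conflict with the statement that the research doctor and the data-entry researcher are unblinded at follow-up. On the natural reading, resting and squeeze pressure, rectal capacity and anorectal sensation are assessed unblinded. This assumes that the research doctor performs or handles those tests at follow-up, which is implied and not stated. The effect on results cannot be sized, and the stated blinding of the physician scoring the Vaizey outcome is not in dispute.

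The allocation point is lesser and conditional. One third of allocations certain and 71% correct guesses are upper bounds. They assume equal allocation, complete and timely knowledge of earlier allocations, and knowledge of block boundaries. They do not show that concealment has failed, and no sample-size figure changes.

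**What to change.** 1. **Preferred:** keep the research doctor and the data-entry researcher blinded at follow-up. The independent assistant already handles allocation, and patients can be asked not to disclose their group to hospital staff.
2. **If that cannot be done:** label pressures, rectal capacity and anorectal sensation as assessed unblinded, and limit the blanket statements in Blinding and in Bias and confounding to the outcomes they cover.
3. **In either case:** state who performs the follow-up tests, and explain how blinded double data-entry fits with the role of the data-entry researcher. Describe the Vaizey score as recorded by a blinded physician from the answers of unblinded patients.
4. **As a precaution only:** if patients remain to be randomized, use varying block sizes, undisclosed to clinical staff, for the rest of the list.

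*Cost.* Items 2 and 3 are changes of wording. Item 1 is a procedural change, probably small, though the article does not say why these roles are unblinded at follow-up. Item 4 needs a regenerated list, a documented change to the randomization procedure, and acceptance of slightly looser balance during recruitment. No extra patients are needed.
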